## Abstract

**Background:**

Hand eczema has a one-year prevalence of approximately 10 % in the general Danish population. Often the disease becomes chronic with numerous implications for the individual’s daily life, occupation and quality of life. However, no guidelines of self-management recommendations beyond the acute stage are given. Self-management of the disease is pivotal and involves self-monitoring of the condition, medication adherence, and preventive behaviour. Interventions best to support the individual in this ongoing process need to be developed.

**Methods/design:**

This paper describes the design of a randomised clinical trial to test a newly developed intervention of individual counselling versus conventional information. 300 patients consecutively referred to dermatologic treatment at two different settings are individually randomised to either the intervention programme, named ‘The Healthy Skin Clinic’ or to the control group. Block-wise randomisation according to setting and gender is carried out.

The intervention offers a tool for self-monitoring; basic and specific individual counselling; the possibility of asynchronous communication with the intervention team; and an electronic patient dialogue forum. Primary outcome variable is objective assessment of the hand eczema severity performed at baseline prior to randomisation, and repeated at six months follow-up. Secondary outcome variables are dermatology related life quality and perceived global burden of disease.

**Discussion:**

The trial aims at evaluating a newly developed guidance programme which is expected to support self-management of patients referred to dermatology treatment due to chronic hand eczema. The design of the protocol is pragmatic with blinding of neither participants nor the investigator. Thus, in the interpretation of the results, the investigator takes into account effects that may be attributed to actors of the interventions rather than the intervention per se as well of potential observer bias. Inclusion criterions are wide in order to increase transferability of the results.

**Trial registration:**

The trial is registered in ClinicalTrials.Gov with registration number NCT01482663.

## Background

Hand eczema is a pruritic inflammatory skin disease characterised in the acute phase by erythema, oedema and sometimes vesicles, while in the chronic state the skin changes are dominated by infiltration, scaling and fissures, which may cause pain. The disease is common 
[1]; in a recent Danish study a one-year prevalence of 14% was found, of which 23% had severe or moderate eczema 
[2]. Hand eczema is not a uniform disease as it exists in a continuum of severity with variations in morphology. Aetiologically, hand eczema may be due to irritant contact dermatitis, which is most prevalent followed by allergic contact dermatitis and atopic hand eczema 
[3]. Multi-causality is frequent and in order to provide adequate treatment and tertiary prevention aetiological factors need to be determined 
[4].

Hand eczema often has a chronic course with symptoms persisting 10–15 years after onset 
[3],5] and with psychosocial consequences such as long term sick leave, involuntary job rotation or early retirement 
[5]. Furthermore, quality of life has been shown to correlate negatively to the severity of the disease 
[4,6]. No consensual definition of chronic hand eczema exists although some authors have used the definition of hand eczema which persists throughout more than three months or which reoccurs twice or more within a 12 month time frame 
[7]. Chronic hand eczema typically has a dynamic course with intermittent eruptions of eczema 
[4]. A guideline for the overall treatment principles for hand eczema has been proposed by the Danish Contact Dermatitis Group 
[4]. However, although chronic hand eczema affects numerous functions in daily life, no specific recommendations as to self-manage the disease beyond the acute stage are given. Patients’ knowledge of their diagnosis may determine their prognosis 
[8]. Also, medical treatment of hand eczema is often prolonged and should be accompanied by skin protection and skin care measures 
[9]. However, some evidence based recommendations of skin protection may be experienced as complex 
[10]. Among dermatological patients it is estimated that 34–45% do not comply with instructions regarding medical treatment 
[11,12]. This may also depend on the satisfaction with and an overall experience of effectiveness of the treatment 
[13]. The patient’s self-management in the course is pivotal as it applies both to handling the acute eczema and to the continuous preventive behaviour, necessary to avoid relapses of the disease. Yet, evidence related to self-management of hand eczema is poor. In chronic illness generally, interventions that aim at increasing medication adherence, and thus indirectly the patient’s self-management, are most effective when intervening in several dimensions 
[14,15]. Better methods to support self-management of patients with chronic hand eczema may potentially improve the prognosis of a disease that is both a burden to the individual and to society. Hand eczema is often caused or aggravated by occupational exposures such as wet work, food handling, cutting oils etc. In several studies, interventions aiming at secondary prevention of occupational irritant hand eczema have been examined 
[16]. Comparisons have been made regarding the usage of protective equipment versus the usage of skin care products 
[17]. Also, the efficiency of skin care programmes including an educational element has been examined. Both skin protection behaviour and objectively assessed symptoms were beneficially impacted in a group of health care personnel 
[18,19] and among employees in the food care industry 
[20,21]. However in general, interventional prevention trials have had methodological weaknesses and insufficient dimensions in terms of power 
[16,18] and only few studies have investigated skin protection programmes as a tertiary preventive measure. In Germany, a combined health educational and health psychological intervention i.e. Tertiary Individual Prevention has been found to significantly increase important factors related to skin protection behaviour 
[22]. This programme requires three weeks of hospitalisation based upon employer-funded health insurance. Hence, these results are not easily transferred to a Danish health care system in which chronic hand eczema is predominantly treated in an outpatient setting. The current randomised controlled trial evaluates the effectiveness of a newly developed nurse-led counselling programme, based upon individual needs and resources, compared to conventional patient information given at medical consultations.

### Theoretical framework and regimen rationale

As aforementioned, chronic hand eczema is characterised by eczematous eruptions occurring in active phases of the disease. Medical treatment, primarily the usage of topical corticosteroids, is required during these eruptions. Periods between eruptions involve restitution of the skin and prevention of future eruptions in the context of daily life when the disease solely is handled as the individual’s self-management. Throughout the course, the individual may adapt to the condition in several dimensions. The progress in disease severity may lead to more apparent symptoms thus influencing the individual’s self-monitoring of the condition. Also, more severe eruptions of eczema may bring about increased involvement from health care professionals. Finally, the prolonged time frame and the repeated relapses can promote changes in the individual’s ability to cope and act upon disease-related problems based on experiences and required knowledge. These patterns of adaptation need to be considered in the support of patients’ self-management.

## Methods/design

### Objectives

The bulk of evidence mostly implies standardised intervention within specific occupational sectors that in particular dispose to hand eczema through wet work. However, in clinical dermatology practice the target group is highly heterogenic involving individuals in different phases of life and living under various conditions all of which may influence their self-management. A need for more individualised action plans and guidance yet still feasible in an institutionalised context has been identified.

The aim of the trial ‘Chronic Hand Eczema - self-management and prognosis’ is to evaluate if a newly developed guidance programme bring about a better prognosis of the disease at six months follow-up in comparison to conventional information.

### Hypotheses

It is hypothesised that the intervention may support the patients’ self-management to a degree that improvement in objectively assessed severity of hand eczema is measurable at a group level at six months follow-up compared to that of a control group. Also, improvement in subjectively assessed severity of disease and quality of life is expected.

### Empirical design

The hypotheses are tested through the conduct of a prospective randomised controlled trial having a pragmatic design 
[23]. The study is a multicenter trial as the setting is an outpatient clinic in a university hospital within the metropolitan area of the Danish capital, Copenhagen (setting A), and a private dermatology practice in Aalborg in northern Jutland, Denmark (setting B). For the purpose of this paper both settings are referred to as ‘the dermatologist’.

### Participants

Consecutive inclusion to the trial is performed. As soon as an individual is referred to treatment at the dermatologist due to ‘hand eczema’, an information letter is posted inviting the patient to participate in the trial. At inclusion, i.e. at first medical consultation at the dermatologist, signed, written informed consent is obtained. An objective evaluation of the present hand eczema is performed prior to an individual randomisation to either conventional information or to guidance according to the intervention. To enhance external validity of the trial, inclusion criterions are wide.

### Inclusion criterions

▪ Patients aged between 18–70 years (hand eczema is frequently work related and individuals older than 70 years may in general have a different pattern of exposure, which has to be considered at inclusion)

▪ A clinical diagnosis of hand eczema given by the dermatologist at the first consultation

▪ Signed, written informed consent to participate

### Exclusion criterions

▪ Patients in need of admittance to the dermatological in-hospital ward at the time of inclusion or during the follow up period

▪ Patients who cannot fill out a questionnaire in Danish due to language difficulties or to a physical or psychological handicap

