### Randomisation

Patients, who fulfil the inclusion criterions, are included consecutively in the trial depending of time of their referral to the dermatologist. A baseline objective evaluation of hand eczema severity is carried out prior to the individual randomisation, which is performed centrally at the National Allergy Research Centre using a computer-generated algorithm unknown to the investigator. The patients are allocated to the intervention group, or conventional information in the control group. The percentage of patients allocated to each group is approximately 50:50. Randomisation is stratified by blocks according to setting and gender, the latter because of a gender ratio of hand eczema, as women have the double risk of men of hand eczema. Also, gender has been shown to impact both performed self-management 
[24] and ‘prescribed’ self-management 
[25].

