### The trial flow

When included in the trial, a baseline questionnaire is handed to the participant. Evidence from randomised trials suggests that in questionnaire design, ‘shorter is better’ 
[26]. Thus, attempts have been made to make the baseline questionnaire as short as possible. However, given the conceptual broadness of ‘self-management’, the questionnaire compiles items covering exposures, susceptibility, knowledge, medical adherence and self-efficacy. Immediately after randomisation, an initial basic counselling is given to participants in the intervention group. An appointment of the subsequent nurse-led consultation is offered to be conveniently executed in timely relation to the next medical consultation. Also, the patient is offered to choose between patient self-management books of either physical or electronic form. The trial flow is displayed in Figure 
1.

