### Statistical methods

All data obtained at baseline will be given a coded ID-number before they are used in further statistical analyses. After double data entry and with the guidance of a statistician, statistical analysis will be performed in SPSS. Stratification for relevant confounders will be performed and descriptive statistics as well as multivariate analyses will be conducted. Ordinal scaled data will be evaluated as to a Gaussian distribution after which between-group differences will be tested in accordance by the use of *t*-test or non-parametric test. Dichotomous efficacy variables are tested by use of chi^2^ test or exact test in case of small numbers. The significance level will be a p-value of less than 0.05.

The final number of patients included in the trial will be reported and intention-to-treat analyses are to be performed meaning all participants will be included in the analysis irrespective of compliance with the intervention protocol. However, an additional per-protocol analysis will also be conducted. Data from patients who refused to participate, dropouts, and loss-to-follow-up participants will be entered to an analysis based upon demographics in order to consider selection bias when interpreting the results. The presentation of the trial results will be according to the CONSORT statement to Trials of Nonpharmacologic Treatment 
[47].

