### Trial duration and discontinuation of individual participants

Duration of patients’ participation will be until follow-up six months after inclusion. It may be that the patient is discharged from treatment prior to date of completion or that dermatological treatment is necessary for a longer period than six months. However, outcome variables will be evaluated at six months follow up and no further intervention will be offered. The participants may continue to use the newly developed website, which is hosted and maintained by the National Allergy Research Centre. This includes access to information; the self-monitoring tool i.e. a personal log as well as the patient dialogue forum.

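### The exclusion criterion on ward admission extends past randomisation and conflicts with the plan to analyse all participants

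*Protocol article*

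**What the plan says.** Under Exclusion criterions, the article lists "Patients in need of admittance to the dermatological in-hospital ward at the time of inclusion or during the follow up period".

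The timing is set out in four other sections:
- Participants: "At inclusion, i.e. at first medical consultation at the dermatologist, signed, written informed consent is obtained".
- Randomisation: "A baseline objective evaluation of hand eczema severity is carried out prior to the individual randomisation".
- The trial flow: "Immediately after randomisation, an initial basic counselling is given to participants in the intervention group".
- Trial duration and discontinuation of individual participants: "participation will be until follow-up six months after inclusion".

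On the analysis set, Statistical methods states that "intention-to-treat analyses are to be performed meaning all participants will be included in the analysis irrespective of compliance with the intervention protocol", and adds that "an additional per-protocol analysis will also be conducted". It also plans a demographic comparison covering refusers, dropouts and losses to follow-up. It makes no exception for patients admitted to the ward. The section on trial duration and discontinuation does not say how such patients are handled.

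**The concern.** An eligibility criterion should be decidable before allocation. Whether a patient will need the ward at some point in the next six months generally is not. If the criterion is used as written, it becomes a rule for taking patients out after randomisation, and the event that triggers it is plausibly related to the outcome. The primary outcome is change in HECSI severity, and the section on theoretical framework and regimen rationale itself says that more severe eruptions may draw in more professional care.

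The intervention is meant to alter severity, so it may also alter who is admitted. Neither patients nor the investigator are blinded, so knowledge of the arm could influence the decision. If fewer intervention patients are admitted, the control arm loses more of its severe cases and a real benefit is understated. If closer contact with the team leads to more admissions in the intervention arm, the benefit is overstated. Two analysts following two different sections of the article could therefore analyse different sets of patients.

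**Working it through.** **Step 1: order of events.** Consent and inclusion take place at the first consultation. HECSI is scored, the patient is then randomised, and basic counselling follows at once in the intervention arm. Follow-up ends six months after inclusion. An admission during follow-up therefore comes after allocation and, in one arm, after exposure to the intervention.

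**Step 2: the two rules side by side.** The exclusion list, read literally, takes the admitted patient out. The intention-to-treat definition keeps every participant. No third passage says which rule governs.

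**Step 3: the plan's own difference.** The sample size section assumes a control mean of 11 (SD 9.0) at six months and a 30% improvement: 0.30 × 11 = 3.3, and 11 − 3.3 = 7.7, the stated intervention mean (SD 6.0). The planned difference of 3.3 is reproduced.

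**Step 4: effect of removing patients.** Let *m* be an arm's mean, *p* the share removed and *h* the mean six-month HECSI of those removed. The mean of those left is (*m* − *p·h*)/(1 − *p*). The article gives neither *p* nor *h*, so both are assumptions.

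| Removed, control v intervention | *h* | Control mean | Intervention mean | Difference | Lost |
|---|---|---|---|---|---|
| 1% v 0.5% | 20 | (11 − 0.2)/0.99 = 10.91 | (7.7 − 0.1)/0.995 = 7.64 | 3.27 | 1% |
| 1% v 0.5% | 40 | (11 − 0.4)/0.99 = 10.71 | (7.7 − 0.2)/0.995 = 7.54 | 3.17 | 4% |
| 5% v 2% | 20 | (11 − 1)/0.95 = 10.53 | (7.7 − 0.4)/0.98 = 7.45 | 3.08 | 7% |
| 5% v 2% | 40 | (11 − 2)/0.95 = 9.47 | (7.7 − 0.8)/0.98 = 7.04 | 2.43 | 26% |

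At 150 per arm, 5% v 2% is 7.5 v 3 patients, and 1% v 0.5% is 1.5 v 0.75.

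**Step 5: the other direction.** With 2% of controls and 5% of intervention patients removed at a HECSI of 20, the means are (11 − 0.4)/0.98 = 10.82 and (7.7 − 1)/0.95 = 7.05. The difference is 3.76, so the benefit is overstated.

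**Step 6: are the inputs compatible with the stated SDs?** The variance between removed and remaining patients is *p*(1 − *p*)(*h* − mean of those left)², and it cannot exceed the arm's total variance. In the most extreme row it is 0.05 × 0.95 × (40 − 9.47)² = 44 for control, below 9.0² = 81, and 0.02 × 0.98 × (40 − 7.04)² = 21 for intervention, below 6.0² = 36. Both are possible. Five per cent of the intervention arm at a HECSI of 40 is not possible: those left would average (7.7 − 2)/0.95 = 6.0, and 0.05 × 0.95 × (40 − 6.0)² = 55, which exceeds 36. An illustration with 5% removed from both arms at 40 therefore contradicts the plan's SD and is not used.

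**Limit of the calculation.** It works on six-month scores, as the article's sample size does, while the primary outcome is change from baseline. If removed patients also started higher, the bias in change would differ.

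**The case against.** The strongest reply is that the article never says that an admitted patient is withdrawn, left unmeasured or dropped from the analysis. The list may have been meant for use at the first consultation, with the phrase about follow-up covering a need already foreseen then. Alternatively, admission might affect only per-protocol status. Statistical methods is the only section that defines the analysis set, and it keeps everyone. Much of this stands. A reader might infer that the plan is bound to discard randomised patients and so breaks the randomised comparison, or that the two rules can never be applied together. The documents support neither. They do leave a literal conflict that nothing resolves, and the foreseen-need reading is not what is written.

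A reader might also infer that admission marks treatment failure, so that the worst outcomes leave the trial. That goes too far. The criterion does not require the admission to be for hand eczema, and a patient admitted and treated early could have any score at six months. This matters for size. If HECSI is taken as gamma-distributed with the plan's means and SDs, and everyone above a common six-month score of 28.7 is removed (5% of controls, 0.9% of the intervention arm), the difference falls to 9.64 − 7.47 = 2.17. That assumes that exactly the highest final scores are lost, which is a worst case the article does not establish.

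Admission may also be rare among outpatients, and then the effect is small. The planned demographic comparison of dropouts and losses shows that selection was considered, but it would not correct for removal related to the outcome.

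**Conclusion.** The point holds as a conflict to reconcile and should be fixed. The conflict itself follows from the text and needs no assumption. Whether any patient would in fact be lost to the analysis depends on how the criterion is read.

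The size is not known. Over the assumed range in the table, the planned difference is understated by 0.03 to 0.87 points (1% to 26%). If admissions were more frequent in the intervention arm, the error would run the other way. These figures show what could happen under stated inputs; they do not estimate what will happen. With the rate unknown and an analysis rule that already keeps all participants, the evidence does not support treating this as a fatal flaw.

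**What to change.** 1. End the criterion at the time of inclusion and remove the reference to the follow-up period. If a need already foreseen at inclusion was meant, say so explicitly.
2. State that a patient admitted after randomisation still has HECSI and questionnaires at six months and is analysed in the randomised arm under intention-to-treat.
3. Report the number of admissions by arm. If anyone has already been taken out on this ground, report those patients by arm too.
4. Confine any exclusion based on admission to the per-protocol analysis.

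This concerns data collection and the analysis set only, and proposes nothing about the care of admitted patients. The target of 150 per group and the planned difference are unchanged. The cost is a short amendment, the prior review and approval that the Trial conduct section requires, and a few six-month assessments that might otherwise not be made.

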### Randomisation

Patients, who fulfil the inclusion criterions, are included consecutively in the trial depending of time of their referral to the dermatologist. A baseline objective evaluation of hand eczema severity is carried out prior to the individual randomisation, which is performed centrally at the National Allergy Research Centre using a computer-generated algorithm unknown to the investigator. The patients are allocated to the intervention group, or conventional information in the control group. The percentage of patients allocated to each group is approximately 50:50. Randomisation is stratified by blocks according to setting and gender, the latter because of a gender ratio of hand eczema, as women have the double risk of men of hand eczema. Also, gender has been shown to impact both performed self-management 
[24] and ‘prescribed’ self-management 
[25].

